**Figure 2. f2:**
[figure not shown]
The schedule of enrolment, interventions, and assessments.

The participants from control group will not receive any messages on any aspects of intervention, neither they will be interacted directly by intervention team throughout the study period. The control group participants will be contacted by the assessors for the baseline and endline assessments only.

There is no anticipated harm from the trial participation. The study participants will be provided with the printed copies of Play Therapy Manuals after completion of trial. The children with below average development scores will receive additional ECD services at hospital ECD centre and will receive follow-up till next one year through home visits.

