### Eligibility criteria

*Inclusion criteria:*
1.Children admitted to the Paediatric Ward of A.V.B.R.H. aged six months to 60 months.2.Children from villages within 25 Km periphery of A.V.B.R.H.3.Parents consenting to the participation of their child in the Play Therapy Programme.

*Exclusion criteria:*
1.Seriously sick, moribund children with life-threatening conditions.2.Children in Intensive Care treatment.

The Investigator will take written informed consent from the parents of the hospitalized children. The comparator (control) group will include children from the adjoining paediatric ward on another floor and admitted during the period when interventions will not be implemented. Children from this group will receive all required treatment and nursing care except the Play therapy sessions. This will help to avoid any contamination. Baseline assessments and socio-demographic information of these children will be collected at enrolment. Follow-up home visits will be done at monthly home visits. Assessments will be done at six months and 12 months from the date of enrolment. If successful, the children from control group will receive play therapy after the trial is over.

The children and their parents signing the informed consent will be enrolled in the study. All enrolled children hospitalized in A.V.B.R.H., scheduled to stay for a minimum of three days in the hospital, will be assigned a Unique ID. Children will be allocated to intervention or control groups using a block randomization process
^
22
^
^,^
^
23
^ with age groups as the blocking variable. Intervention group will receive the play therapy sessions along with the required treatment and nursing care during hospitalization stay. Sociodemographic profile and baseline assessments will be done. Play therapy sessions will be conducted at the dedicated play area in hospital. Also, these children from the intervention area will receive the play sessions at scheduled monthly home visits.
Figure 1 shows the anticipated Consort Flow Diagram of study participants.

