### Outcomes

*Primary outcomes:*
1.Improvements in mean scores of child developmental parameters for cognitive, physical, socio-emotional, and language development by the end of one year of intervention.2.Improvements in knowledge and skills of parents regarding early child development by the end of one year of intervention.

*Secondary outcomes:*
1.Improvements in the parent-child satisfaction levels regarding the in-hospitalization care and follow-up by the end of one year of intervention.

Figure 2 details the schedule of enrolment, interventions, and assessments.

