### Data collection and management

Data will be collected in pre-tested Open Data Kit (O.D.K.) based app with inbuilt checks for data quality, identifying duplicate entries. The data received on dedicated server of Research Cell of Datta Meghe Institute of Medical Sciences will be imported and checked on real time basis. The data will be encrypted for sensitive information and will be handled by the assigned team including Information Technology Coordinator and statistician. The datasets will be shared and made reusable according to FAIR data principles.

Assessments will be conducted using the tools as detailed below:
1.Physical Development (Using Developmental Milestones Checklist-II)
^
27
^
^,^
^
28
^
a.Improvement in Fine Motor scoresb.Improvement in Gross Motor scores2.Cognitive Development Scores (Using Developmental Milestones Checklist-II)3.Language Development Scores (Using Developmental Milestones Checklist-II)4.Socioemotional Development Scores (Using Profile of Socio-emotional Development)
^
29
^
5.Home Environment (Using HOME Inventory Assessment)
^
30
^
^–^
^
32
^
6.Parent-child Interactions (Using Observation of Mother-Child Interaction Tool)
^
33
^

The research assistants will be trained on the use of all these tools and inter-rater, intra-rater scoring exercises will be conducted during training. To promote participant retention and complete follow-up, all enrolled children in the intervention group will receive scheduled home visits at monthly intervals. The children in the control group will be followed up telephonically at monthly intervals. Also, telephonic follow-up will be taken for those missing home visits in intervention group. The outcome data will detail the participants who discontinue or deviate from intervention protocols.

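### Follow-up contact with control families is stated inconsistently in three places; if the baseline-and-endline rule is followed, only the intervention arm is traced monthly before the 12-month outcome

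*Protocol article*

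**What the plan says.** Three parts of the protocol article's current text deal with contact with controls after enrolment.

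- **Eligibility criteria**, in the paragraph that introduces the comparator group: "Follow-up home visits will be done at monthly home visits" and "Assessments will be done at six months and 12 months from the date of enrolment". Neither sentence names an arm. The sentences on either side of them are about control children.
- **Criteria for group sessions at the hospital**, text after Figure 2: "The control group participants will be contacted by the assessors for the baseline and endline assessments only". The sentence before it bars the intervention team from contact with controls: "neither they will be interacted directly by intervention team throughout the study period".
- **Data collection and management**: "The children in the control group will be followed up telephonically at monthly intervals". For the other arm the same paragraph says that "all enrolled children in the intervention group will receive scheduled home visits at monthly intervals", and it gives retention and complete follow-up as the purpose.

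The Outcomes section places the primary child outcome at one year: "Improvements in mean scores of child developmental parameters for cognitive, physical, socio-emotional, and language development by the end of one year of intervention". No six-month outcome is listed.

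**The concern.** Depending on the passage followed, a control family has about 12 home visits, about 12 telephone calls, or no contact between baseline and endline. It either has or lacks a six-month score.

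The risk is to the 12-month comparison. The intervention arm has monthly visits that the article itself presents as a retention measure. If controls have no counterpart for a year, they are the more likely arm to be lost, and the families lost may differ from those retained. Statistical methods plans imputation for families that cannot be traced; under the baseline-and-endline rule, a lost control child has only baseline data to impute from. The delivery section also uses the monthly home visits to assess the home environment and parent-child interaction, so whether controls are visited decides whether interim data of that kind exist in both arms.

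**Working it through.** **Comparing the passages in pairs**

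1. *Eligibility criteria against the text after Figure 2.* Monthly visits plus a six-month assessment cannot be squared with assessor contact at baseline and endline only. If the Eligibility sentences are meant for both arms, controls are still included and the conflict stays.
2. *Eligibility criteria against Data collection and management.* These differ on mode: home visits or telephone. The second section gives home visits to the intervention arm and calls to controls.
3. *Text after Figure 2 against Data collection and management.* The first limits what the assessors do and bars the intervention team. The second does not say who telephones. Both can be followed only if a third party calls, and none is named. This pair is an ambiguity rather than a flat contradiction.

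**When contact differs between arms**

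- Eligibility text, read as covering controls: monthly visits in both arms, so visit frequency does not differ.
- Data collection text: monthly visits against monthly calls.
- Text after Figure 2: monthly visits against nothing until endline.

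**Planned effect (Sample size section)**

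Inputs: difference 0.5, SD 1.69, 1.96 and 0.84. n = 2 × (1.96 + 0.84)² × 1.69² / 0.5² = 179.13, which rounds up to the stated 180 per arm (the article prints 179.37 after rounding 1.69² to 2.86). The planned standardised difference is 0.5 / 1.69 = 0.296 SD.

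**Illustration of bias from unequal loss**

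The loss rates and the 0.3 SD are assumptions; the article gives neither. If a fraction L of an arm is lost and lost children score 0.3 SD below retained ones, the retained mean exceeds the full-arm mean by 0.3 × L.

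- Control, 20% lost: 0.20 × 0.3 = 0.060 SD
- Intervention, 5% lost: 0.05 × 0.3 = 0.015 SD
- Intervention minus control is therefore understated by 0.060 − 0.015 = 0.045 SD, and 0.045 / 0.296 = 15% of the planned difference. The direction is towards the null.

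Range, with the same 0.3 SD: equal loss gives 0; a gap of 10 percentage points gives 0.10 × 0.3 = 0.030 SD; a gap of 20 points gives 0.20 × 0.3 = 0.060 SD. If lost children score higher than retained ones, the sign reverses. These figures are for an analysis of retained children; imputation would reduce the bias to the extent that the data collected predict the missing scores.

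**Does unequal loss also cost power?**

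- 5% and 20% lost, 171 v 144: 0.2959 × √(171 × 144 / 315) = 2.616; Φ(2.616 − 1.96) = 74.4%
- Same total loss split equally, 157.5 per arm: 0.2959 × √(157.5 / 2) = 2.626; Φ(2.626 − 1.96) = 74.7%

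Almost all of the fall from 80% comes from total loss, not from its imbalance.

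**The case against.** The strongest reply is that only part of the text truly conflicts. The telephone sentence is in the passive and stands beside the sentence on retention, so calls by other staff would respect the text after Figure 2. The Eligibility sentences are clumsy and name no arm. Figure 2, the schedule, is not available here and may show which scheme applies. Statistical methods also says that families with missing data will be contacted by home visit, which is some safeguard in both arms.

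Much of this stands, but it does not clear the text. The third-party caller has to be supplied by the reader, the Eligibility sentences conflict with the other two passages on any reading that includes controls, and a figure would not remove conflicting prose. Visits made once data are already missing help only for families that can still be found.

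A reader might infer more than the article supports:

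- *That the comparator is undefined.* It is not. Eligibility criteria gives controls all required treatment and nursing care without play therapy. Only follow-up contact is unsettled.
- *That attention and retention effort necessarily differ by arm.* They do under the second and third passages, not if both arms are visited monthly.
- *That a planned six-month comparison is lost.* None is listed. The delivery section and Outcomes point to one year, and the allocation and statistical sections speak of baseline-endline and pre-post data.
- *That this inconsistency costs about six points of power.* The calculation shows that the fall belongs to total attrition. The 180 per arm has no reserve for the stated 10% dropout (180 / 0.90 = 200), but that is a separate sample-size matter.

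**Conclusion.** The inconsistency is real and stands in current text, so the control follow-up cannot be carried out as written. It should be corrected.

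The consequence is conditional. If the baseline-and-endline rule is the one applied, tracing is monthly in one arm and absent in the other for a year, and the 12-month primary comparison is exposed to differential loss. Monthly calls would narrow that gap; monthly visits in both arms would largely close it. The article's own figures cannot size the bias. The 0.045 SD towards the null rests wholly on assumed losses of 5% and 20% and an assumed 0.3 SD deficit, and should be read as an order of magnitude only.

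**What to change.** Reconcile the three passages into one rule that states, for each arm, who makes contact, how and when.

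- Keep the monthly retention call for controls from Data collection and management. State that it is made by staff outside the intervention team and carries no developmental content.
- Amend the words limiting controls to baseline and endline contact, and the home-visit sentence under Eligibility criteria, so that both match.
- Assess both arms at the same time points, with the same tools and blinded assessors: baseline and 12 months, and six months only if it is done in both arms. Otherwise remove the six-month assessment and claim no between-arm result at six months.

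Trial status gives recruitment from January 2023 and expected completion on 30 May 2024, and the protocol version is dated 04/10/2024, so follow-up may be over. In that case, state which scheme was actually used and report contacts and losses by arm.

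The cost is mainly wording, since the calls are already in the article. Calls give controls slightly more attention. A six-month assessment in both arms could add work in the intervention arm, which is why it is left conditional.

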### Outcomes

*Primary outcomes:*
1.Improvements in mean scores of child developmental parameters for cognitive, physical, socio-emotional, and language development by the end of one year of intervention.2.Improvements in knowledge and skills of parents regarding early child development by the end of one year of intervention.

*Secondary outcomes:*
1.Improvements in the parent-child satisfaction levels regarding the in-hospitalization care and follow-up by the end of one year of intervention.

Figure 2 details the schedule of enrolment, interventions, and assessments.

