### Sample size

With reference to the study conducted by Gaidhane
*et al.,
*
^
25
^
^,^
^
26
^ the expected difference in child development outcomes between the intervention and control groups is 0.5 SD, considering a dropout rate of 10%, level of significance = 5%, and power = 80%. The formula for calculating sample size for two independent means is:

$$n=\frac{2\;{\left(\mathrm{Z\alpha}+\mathrm{Z\beta}\right)}^{2}\times \delta^{2}}{d^{2}}$$
where

n = Minimum sample size required in each group,

d = Expected mean difference between two groups = 0.5

δ = standard deviation = 1.69 (As per Previous Study)

Zα: value of type I error at 5% significance level =1.96

Zβ: value of type II error at 80 % Power (1-β) = 0.84

Based on the above formula, the calculations are as follows:

$$\begin{array}{c} n=\frac{2\;{\left(1.96+0.84\right)}^{2}\times 1.69^{2}}{{\left(0.5\right)}^{2}}\\ =\frac{2\left(7.84\right)\times 2.86}{0.25}\\ =\frac{44.84}{0.25}=179.37\approx 180 \end{array}$$

Thus, the sample size required per group is 180. Hence total sample size required is 360. A sample size of 360 subjects, 180 in each arm, is sufficient to detect a difference of 0.5 between groups in developmental scores, assuming a standard deviation of 1.69 using a two-tailed t-test of difference between means with 80% power and a 5% level of significance. For assessing the changes in parenting knowledge and skills, parents of all children in intervention group
**(180)** will be assessed.

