### Statistical methods

After appropriate cleaning and compilation, the pre- and post-intervention child development data in specified domains will be collected and fed to STATA-14 by the assigned statistician. Individual and child age-group wise scores of developments will be calculated and tabulated. Mean differences in child development scores for intervention and control groups and pre-post intervention will be calculated. The effect size by Cohen’s-D will be calculated for each child age group, and significance of differences in effect size will be estimated. Also, qualitative subgroup and adjusted analyses, Difference in difference analysis for motor, language, cognitive and socio-emotional development scores will be done. Attempts will be undertaken to ensure the collection of complete data. In cases of missing data, families will be contacted through home visits and missing data will be collected. If any case/family could not be tracked, iterative algorithm or multiple imputation technique will be used to handle the missing data. The datasets analysed during the current study, statistical code and full protocol will be made available by publishing on open data repository Zenodo.

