## Discussion

When a child is engaged in play activities it plays an important role in decreasing the stress of parents and children. As the studies suggest, play stimulation can play an important role in relieving the symptoms of stress and organic diseases. The hospital staff needs to be trained; play stimulation should occur in the wards, and counselling should be given to the parents and their children to release their stress. Before the play stimulation activities should be practiced, the caregivers, therapists, hospital staff, and parents must understand what is expected in different age domains related to cognitive and psychosocial development.

This play therapy intervention package for hospitalized children will be tested for its effectiveness in the Acharya Vinoba Bhave Rural Hospital, Wardha, India. The data of changes in child development parameters will be analysed. If this trial is successful to bring out positive changes in child development parameters of intervention group compared to control group, it can prove to be an evidence-based proof of concept for the future ’Play Therapy Stimulation Package’ for hospitalized children. If the trial fails to bring-out improvements in child development parameters in intervention arm compared to control arm, the gaps and deficiencies will be explored and attempts will be done to reframe the trial for reimplementation. As this will be a single centre study, the response rate and acceptance of intervention by beneficiaries may need to be generalizable to different types/levels of inpatient childcare facilities. A minimum of three days hospital stay is expected with the initial play therapy start. Staying for less time than this duration may not effectively stimulate children and sensitize parents. Also, follow-up after discharge may pose some challenges.

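### Four developmental domains are primary with no lead domain and no any-or-all rule, so the single-test 5% and 80% behind the sample size do not define the error rate or power of the trial's success claim

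*Protocol article*

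**What the plan says.** All references are to the protocol article.

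- **Outcomes.** The first primary outcome is "Improvements in mean scores of child developmental parameters for cognitive, physical, socio-emotional, and language development by the end of one year of intervention". No domain leads, there is no composite, and nothing says how many domains must improve. Parent knowledge and skills form a second primary outcome.
- **Sample size.** The basis is "level of significance = 5%, and power = 80" percent, "using a two-tailed t-test of difference between means with 80% power and a 5% level of significance". The result, 180 per arm, "is sufficient to detect a difference of 0.5 between groups in developmental scores". Which score this means is not stated. The effect appears twice: the text says the expected difference in "child development outcomes between the intervention and control groups is 0.5 SD", and the formula uses "d = Expected mean difference between two groups = 0.5" with a standard deviation of 1.69.
- **Data collection and management.** Physical development is recorded as a fine motor and a gross motor score.
- **Statistical methods.** Difference-in-difference analyses are planned for motor, language, cognitive and socio-emotional scores. Cohen's d is planned for each age group, and "significance of differences in effect size will be estimated". No significance level is given for any individual test.
- **Discussion.** The success statement begins "If this trial is successful to bring out positive changes in child development parameters of intervention group compared to control group" and goes on to describe the package as an evidence-based proof of concept.
- **Trial design.** The trial is called exploratory.

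**The concern.** A 5% level and 80% power have meaning only for a defined claim. Here they belong to one comparison, while the claim may rest on any of four primary domains or on all of them. Which rule applies could be settled after the results are known.

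The two rules fail in different ways. If one significant domain is enough, the chance of declaring success for an ineffective programme exceeds 5%. If every domain must be significant, that chance stays below 5%, but the trial can miss a real effect much more often than 80% power implies. A reader of the results could not tell which operating characteristics the trial had.

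**Working it through.** **Inputs from the protocol.** Two-sided alpha 0.05; power 0.80; difference 0.5; SD 1.69; 180 per arm; four primary domains (Outcomes and Statistical methods).

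**Assumption.** The correlation between domain scores is not given. It is varied from 0 to 0.8 and taken as equal for every pair.

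**1. The plan's own figure.** n = 2 × (1.96 + 0.84)² × 1.69² / 0.5² = 179.13 per arm, which rounds up to 180. The protocol prints 179.37 because it rounds 1.69² to 2.86. The figure of 180 is right for one test. The standardised effect is 0.5/1.69 = 0.296 SD, and the test statistic has expected value 0.296 × √(180/2) = 2.81. Power is Φ(2.81 − 1.96) = 80.1%.

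**2. Any one of four domains suffices, each at 5%.** With independent scores and no true effect, the chance of at least one significant result is 1 − 0.95⁴ = 18.5%. For correlated scores the figures come from simulated equicorrelated normal statistics (1,000,000 draws).

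**3. All four domains required, each at 5%.** The false-claim chance cannot exceed 5%. With 0.296 SD in every domain and independent scores, power is 0.801⁴ = 41%. Correlated cases come from the same simulation.

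| Correlation | Any one of four: false-claim chance | All four: power |
|---|---|---|
| 0 | 18.5% | 41% |
| 0.3 | 17.4% | 50% |
| 0.5 | 15.6% | 56% |
| 0.7 | 13.0% | 62% |
| 0.8 | 11.4% | 66% |

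**4. Fine and gross motor counted separately (five scores).** The false-claim chance is 1 − 0.95⁵ = 22.6% if independent and about 13% at correlation 0.8. Power for all five runs from about 33% to 64%.

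**5. Power under Holm with four domains.** The first step uses alpha 0.05/4 = 0.0125, critical value 2.498.
- At 0.296 SD with 180 per arm: Φ(2.807 − 2.498) = 62%.
- At 0.5 SD with 180 per arm: 0.5 × √90 = 4.743, and Φ(4.743 − 2.498) = 98.8%.
- With the stated 10% dropout, 180 × 0.9 = 162 per arm: Φ(2.663 − 2.498) = 57% at 0.296 SD, and 97.7% at 0.5 SD.

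**6. Sensitivity to the effect size.** If the true effect were 0.5 SD in every domain, single-test power would be 99.7%, and even the all-four rule with independent scores would have power 0.997⁴ = 98.9%. The loss of power in step 3 therefore depends on the formula's 0.296 SD. The inflation in step 2 does not depend on the effect size.

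**The case against.** **The article condenses a fuller plan, and multiplicity procedures usually sit in an analysis plan.** This stands for the mechanics of adjustment. It does not cover what the article itself fixes: the set of primary domains, the alpha and power behind 180 per arm, and the success statement. Those do not fit together.

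**The trial is exploratory and aims only at proof of concept.** This stands in part and lowers the severity. The same article nevertheless presents a formal 5% and 80% calculation and an evidence claim.

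Several stronger readings are tempting, but the document does not support them:

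- *Each domain is tested at 5%, and one significant result counts as success.* The 5% level appears only under Sample size, and the Discussion sentence is conditional, plural prose with no decision rule. The 11-19% describes one possible reading.
- *There are five primary tests.* Outcomes and Statistical methods list four domains. Fine and gross motor are sub-items in the data-collection list.
- *Parent knowledge adds a further between-arm test.* Under Sample size it is assessed in intervention-arm parents only, so as written it is not a between-arm comparison.
- *Each age group brings a further set of tests that could carry the claim.* The sentence on significance of effect-size differences may mean a comparison between age groups, and nothing says that one age group alone would count as success.

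A single composite would also hold the 5% level. However, it would pool two instruments and replace the primary outcome late in the trial, so it is not the preferred remedy.

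**Conclusion.** The point holds as a missing decision rule. With four primary domains and a sample size for one unspecified score, the trial-level error rate is undefined. At the formula's inputs, neither simple rule delivers both stated figures: any one of four gives a false-claim chance of about 11-19%, and all four gives power of about 41-66%. The ranges rest on assumed equal correlations of 0 to 0.8 and full follow-up, and the power range also assumes the same 0.296 SD shift in every domain. If the effect is 0.5 SD, as the text also says, power is ample under either rule and only the any-one error rate remains a problem. This should be corrected, but given the exploratory label it does not undermine the trial.

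**What to change.** 1. In Outcomes and Statistical methods, state that the 12-month between-arm differences in the four domains are tested with Holm's procedure at a family-wise two-sided 5%. Alternatively, name one domain as primary and make the others secondary. Say how the fine and gross motor scores form the physical domain.
2. In the Discussion, limit the success wording to domains that are significant under that rule.
3. Treat age-group results as supportive, assessed through an arm-by-age-group interaction.
4. In Sample size, restate the power for 180 per arm with full follow-up: about 62% per domain at the first Holm step for 0.296 SD, or about 99% for 0.5 SD. Say which effect is meant.

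**Cost.** Wording and a restated power figure; no new data and no extra enrolment. An effect confined to one domain could no longer be claimed at an unadjusted 5%. Timing also matters: Trial status gives recruitment from January 2023 and expected completion on 30 May 2024, and the protocol version is dated 04/10/2024. If outcome data have already been unblinded, the rule must be reported as post hoc.
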